### Acknowledgement of selection bias

The liver metastases multidisciplinary team meeting at the Manchester Royal Infirmary is the sole forum approved by cancer commissioners for discussion of the care of patients with colorectal cancer liver metastases. The HPB unit guideline is that all patients with stage IV colorectal cancer should have their care reviewed at the MDT. However, it is acknowledged that there are several groups of patients who may bypass the MDT. In particular, patients with systemic disease ‘beyond liver’ may be referred for chemotherapy without consideration for liver surgery. From the patient’s perspective, this care pathway is appropriate. Similarly, patients who present to local MDTs with liver metastases who undergo bowel-first surgery but whose disease progresses rendering them unsuitable for consideration for liver surgery will likely not be referred. For the purposes of reporting the CoSMIC data, these sources of patient loss to study will be acknowledged together with any potential for selection bias. Reporting will be pragmatic and descriptive.

### Statistical methods

Summary characteristics of patients, patient care provided and patient outcomes reported. Treatment centre characteristics will include measures of activity and surgical preference.

Exploratory analysis of process and clinical outcomes will be undertaken to explore the influence of patient, clinician, centre and treatment covariates, using regression modelling. Models will be subject to specification and robustness checks. Standard Generalised Linear Models (GLIM) and propensity score matching approaches will be compared with explore potential spectrum bias issues.

Interview transcripts will be managed by NVivo (QSR International, Melbourne, Australia) software. Interviews will be analysed thematically, using constant comparison^35^ within a modified framework approach^36^ coding both ‘horizontally’ (by coding each interview as a standalone hermeneutic unit) and ‘vertically’ (by scanning across the interviews for specific terms). Identified categories will be developed into a matrix of themes using mind-mapping techniques and a systematic cross-comparison will be undertaken to identify the similarities and differences between the different types of participant.

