**Methods and analysis:**

Colorectal cancer with Synchronous liver-limited Metastases: an Inception Cohort (CoSMIC) is an inception cohort study of patients with a new diagnosis of colorectal cancer with synchronous liver-limited metastases. The sequence of treatment received, and factors influencing treatment decisions, will be evaluated against European Society of Medical Oncology guidelines. Clinical data will be collected, and quality of life, morbidity, mortality and long-term outcome compared for different treatment sequences adjusted for prognostic factors. Disease-free survival or progression will be measured at 1, 2 and 5 years. A nested qualitative study will ascertain patient experiences and clinician perspectives on delivery of care.

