### Setting

The study population will comprise patients with colorectal cancer with liver-limited hepatic metastases referred to the Hepatobiliary Surgical Unit at Manchester Royal Infirmary—an NHS regional cancer-network approved hepato-pancreato-biliary (HPB) centre with a formally constituted and National Cancer Network peer-review accredited MDT. The study opened for recruitment in April 2015 with prospective recruitment to be undertaken for 24 months.

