#### Disease-free survival 12 months after enrolment into protocol

This is defined as the absence of tumour on a CT scan of the thorax, abdomen and pelvis undertaken at the completion of the protocol. In the case of those patients with rectal tumours treated by a’ watch and wait ‘policy, the term disease free can only be applied if there is a combination of radiological, endoscopic and clinical evidence of absence of cancer.

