#### Mortality

Overall and cancer-related mortality in either arm after enrolment will be recorded. Mortality (and cause) will be determined using the Demographics Batch Service to access the national electronic database of the UK NHS.

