### Data sources and measurements

Data will be collected prospectively using electronic study clinical case report forms. These will be anonymised and encrypted for storage and analysed prospectively during study to maximise data completion and resolve emergent problems in a timely fashion. The principal source of data will be the individual patient records. In addition, information will be gained by direct interview with patients (for quality of life assessment) and by interview with clinicians (for MDT choice decisions). Vital status beyond the duration of the study will be determined through the Demographics Batch Service of the NHS. Data will be reported at the end of year 3 allowing for a minimum 12 months outcome data in the entire cohort. It is also proposed (contingent on separate funding) that information on outcome will be collected for up to 5 years from study commencement, providing an informative survival analysis of treatment options.

Qualitative interviews will be audio recorded and transcribed verbatim.

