### Study size

Based on clinical registers, the HPB unit at Manchester Royal Infirmary sees approximately 75 patients with colorectal cancer with synchronous liver-limited hepatic metastases per annum. As there are no study-related interventions, recruitment rates should be high and dropout low and is estimated to provide 150 patients in the 2-year recruitment period. A formal power calculation is not provided for this inception cohort study. Instead, the sample size is informed by the need to: provide stable estimates of variance for a range of outcomes; explore the relationship between the treatment pathway and health outcomes; estimate acceptability and recruitment rates; and describe patient and clinician experiences.

Purposeful sampling will be used to select patients from the cohort for the qualitative study. It is estimated that a sample size of four to six patients per group and one to two clinicians will produce data saturation. However, we will continue to interview until data saturation is reached.

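### Disease-free survival is fixed as a scan status at set times and no funded time-to-event analysis is named, although follow-up at the year-3 report runs from 12 to 36 months

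*Protocol article*

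**What the plan says.** The Abstract of the protocol article states: "Disease-free survival or progression will be measured at 1, 2 and 5 years". Box 1 (Data collection) and the Dissemination policy repeat those time points.

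The section on disease-free survival 12 months after enrolment gives the only definition of that outcome: "This is defined as the absence of tumour on a CT scan of the thorax, abdomen and pelvis". The scan is the one done when the treatment protocol is completed. The definition gives no date of recurrence or progression and does not mention death.

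On mortality the article says: "Overall and cancer-related mortality in either arm after enrolment will be recorded". It sets no time cut there, and deaths are traced through a national NHS service.

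Statistical methods announces exploratory regression modelling and adds: "Standard Generalised Linear Models (GLIM) and propensity score matching approaches will be compared". It names no method for censored data.

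The calendar is given in two places. Setting says: "The study opened for recruitment in April 2015 with prospective recruitment to be undertaken for 24 months". Data sources and measurements says: "Data will be reported at the end of year 3 allowing for a minimum 12 months outcome data in the entire cohort". The latter section also proposes collecting outcomes for up to 5 years from the start of the study, to support a survival analysis, but only if separate funding is found.

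**The concern.** Death, recurrence and progression are dated events, and patients enter over two years. At one common reporting date they have been followed for different lengths of time. A status read at a fixed time handles this poorly in two ways. At 12 months everyone can be classified, but all later events are ignored. At 24 months the later-enrolled patients cannot be classified at all, although the Analysis plan section says that all patients will contribute outcomes to the analyses.

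Comparative outcome data by surgical sequence is a primary aim. The cohort is at most about 150 patients in three non-randomised groups, and the results may inform a definitive trial. Information given up here widens intervals that will be wide anyway.

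**Working it through.** **Inputs from the article.** The unit "sees approximately 75 patients with colorectal cancer with synchronous liver-limited hepatic metastases per annum" and recruitment is "estimated to provide 150 patients in the 2-year recruitment period". Check: 75 × 2 = 150, which agrees. Recruitment lasts 24 months and the report is at month 36.

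**Follow-up at the report.** A patient enrolled in month m has 36 − m months. With m from 0 to 24 this gives 36 down to 12 months. A full 24 months needs m ≤ 12, which at a steady rate is 12/24 × 150 = 75 patients. The other 75 have no 2-year status. For the proposed extension to 5 years from study start, follow-up is 60 − m, or 36 to 60 months, so almost nobody reaches 5 years from enrolment.

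**Assumptions (not in the article).** Exponential event times with yearly hazard λ; uniform accrual; two groups compared; two-sided 5% level; hazard ratio (HR) 0.5 to 0.8; 100 or 150 patients analysed; split 50:50 or 80:20; reference-group 12-month event rate 20% to 70%, or a hazard taken from the 25% to 40% 5-year survival that the Background gives for resectable disease.

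**Formulas.**
- Event by 12 months: 1 − e^(−λ).
- Event seen by month 36 (censoring uniform from 1 to 3 years): 1 − (e^(−λ) − e^(−3λ))/(2λ).
- Time-to-event power: Φ(√(D·a(1−a))·|ln HR| − 1.96), with D events and share a in one group.
- 12-month power: two-proportion test with pooled variance under the null.

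**One case worked through: 12-month rate 40%, HR 0.6, 75 v 75.**
- λ₀ = −ln 0.6 = 0.511; λ₁ = 0.6 × 0.511 = 0.306.
- By 12 months: 0.400 and 0.264, so 75 × 0.664 = 50 events.
- By the report: 0.624 and 0.450, so 75 × 1.074 = 81 events. Ignored: 1 − 49.8/80.5 = 38%.
- Time-to-event power: √(80.5 × 0.25) × 0.511 = 2.29; Φ(2.29 − 1.96) = 63%.
- 12-month status: difference 0.136, null standard error 0.077, alternative standard error 0.076; Φ((0.136 − 1.96 × 0.077)/0.076) = 42%.
- 24-month status on the 75 patients who have it: 35%.

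A simulation of this case gave 63% for both the log-rank test and a Poisson GLM with a follow-up offset, against 44% for logistic regression on 12-month status.

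**Other cases (HR 0.6, 75 v 75).**

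| 12-month rate | Events by 12 months / by report | Ignored | Power, status v time-to-event |
|---|---|---|---|
| 30% | 37 / 63 | 42% | 33% v 53% |
| 40% | 50 / 81 | 38% | 42% v 63% |
| 50% | 63 / 96 | 34% | 51% v 71% |
| 70% | 91 / 122 | 25% | 65% v 81% |

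With 75 v 75 and 12-month rates of 20% to 70%, the difference is 8 to 14 points at HR 0.7 and 4 to 6 points at HR 0.8. Over the whole grid, 22% to 46% of events are ignored and the power difference is 2 to 33 points.

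**The case against.** The strongest objection is that the criticised analysis is not written down. A reader might infer that the plan fits logistic models to 12-month yes/no status. The article does not say so. It speaks of regression modelling in general and names GLMs in a comparison with propensity matching. A GLM can use person-time, and a Poisson model with an offset performs as well as the log-rank test. Naming GLMs is therefore not an error.

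A reader might also apply the loss to mortality. The Mortality section sets no 12-month cut, so figures for deaths dichotomised at 12 months would price an analysis that nobody has proposed. The 25% to 40% survival figure concerns resectable disease, which eligibility does not require.

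Nor can one loss figure, such as 40% of events or 20 points of power, be attached to this study. Values of that size arise at some assumed hazard ratios and event rates and not at others. The article gives no effect size, group shares or disease-free survival rate. It declines a formal power calculation and calls the modelling exploratory. Finally, Cox or Kaplan-Meier detail may sit in an analysis plan that is not shown.

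All of this stands as a limit on the claim. What it does not remove is the stated definition. Disease-free survival is fixed as a scan status, whereas failure to complete treatment is explicitly timed in days from enrolment. The only survival analysis mentioned is conditional on funding. An unseen plan would have to override that definition, not merely fill it in.

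**Conclusion.** The point holds in a limited form. The disease-free survival definition and the fixed reading times fit badly with follow-up of 12 to 36 months, and the article commits to no censored-data analysis for the year-3 report. That about half the cohort lacks 2-year status follows from the article's own calendar, assuming steady recruitment. The loss from using 12-month status alone is conditional: 22% to 46% of events and 2 to 33 points of power under the listed assumptions. It is a loss of precision and not of a promised power. It would also shrink if a landmark removed early events from the time-to-event comparison. The change is worth making because a dated, censored outcome is better in every scenario examined and costs little.

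**What to change.** In the disease-free survival section and in Statistical methods:

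- Define disease-free/progression-free survival (progression, recurrence or death) and overall survival as time-to-event outcomes on all available follow-up, censored at last contact or data cut. State the time origin, since patients have disease at enrolment.
- Record the date of the first imaging that shows progression or recurrence.
- Report 1- and 2-year results as Kaplan-Meier estimates.
- Compare sequences with a Cox model, or a Poisson GLM with log follow-up time as offset, using the planned prognostic adjustment.
- Because groups are formed by the sequence actually received, which is known only after enrolment, use a landmark or time-varying treatment. A model from enrolment by completed sequence would credit patients with the time they had to survive to complete it.
- Align this wording with the survival analysis in Data sources and measurements, so that the year-3 report does not depend on the extra funding.

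The cost is analysis wording and, if not already captured, one date field from routine imaging reports; mortality is already traced nationally. There are three downsides: progression dates follow routine scan timing, proportional hazards must be checked, and a landmark excludes early events.

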### Recruitment

Patients will be formally identified prospectively at the weekly regional HPB MDT and approached in the outpatient clinic at MRI to discuss participation. Recruitment began in April 2015. For patients wishing to enrol, but where the treatment pathway has already started (typically those who presented with an acute abdomen secondary to the bowel lesion), data will be retrospectively collected on treatment already received. Missing data points, particularly quality of life prior to surgery, during data analysis will be compensated for by unit imputation.

Potential participants of qualitative study will be approached following completion of their treatment either in the outpatient clinic or by telephone to ascertain their interest in taking part in the interviews.

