### Analysis plan

The care of patients within the study pathway will be characterised by their principal treatment route as synchronous, liver first or bowel first. All patients will provide outcomes which will be included within analyses, grouped according to the treatment sequence received. Complication profiles in patients according to treatment group will be reported.

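### Comparing GLM with propensity matching tests model dependence and overlap only; it cannot reveal or bound the referral loss and late entry that the protocol itself describes

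*Protocol article*

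**What the plan says.** The Statistical methods section describes exploratory regression modelling of process and clinical outcomes, then adds: "Standard Generalised Linear Models (GLIM) and propensity score matching approaches will be compared with explore potential spectrum bias issues". The only other check named is general: "Models will be subject to specification and robustness checks".

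The Analysis plan section assigns patients to synchronous, liver-first or bowel-first, "grouped according to the treatment sequence received". The Abstract promises that outcomes will be compared between sequences with adjustment for prognostic factors, and the Aims section lists comparable outcome data by sequence among the primary aims.

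Two other sections bear on who enters that comparison. Under Acknowledgement of selection bias, patients at local MDTs "who undergo bowel-first surgery but whose disease progresses rendering them unsuitable for consideration for liver surgery will likely not be referred". The stated handling is that "these sources of patient loss to study will be acknowledged together with any potential for selection bias", followed by "Reporting will be pragmatic and descriptive". Under Recruitment, patients may enrol "where the treatment pathway has already started", typically after an acute abdominal presentation, with earlier treatment data collected retrospectively.

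**The concern.** The comparison of two adjustment methods is the only specific analytic step that the protocol ties to spectrum bias. Both methods see the same rows and the same covariates. A patient who had bowel-first surgery, progressed and was never sent to the regional MDT is in neither analysis. A patient who enrols after bowel surgery has already come through the period in which such losses occur, and the timing outcomes and the 12-month disease-free outcome run from enrolment. A prognostic judgement made at the MDT but not recorded is absent from both models.

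The protocol describes the study as the first direct prospective comparison of surgical sequences and expects it to guide later studies, including randomised ones. If the two methods gave similar answers, a reader could take that as support for the sequence comparison on exactly the point where the comparison is uninformative.

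**Working it through.** **The plan's own figure.** The Study size section gives about 75 patients a year for 2 years: 75 × 2 = 150, which reproduces. There is no power calculation to check. The protocol gives no referral-loss rate, outcome rate or group split, so everything below is assumed.

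**Step 1: closed form for referral loss.** Let p be the true disease-free proportion, equal in both groups, and f the share of failing bowel-first patients who are not referred. The proportion observed in bowel-first is

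p′ = p / [p + (1 − p)(1 − f)].

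With p = 0.5 assumed:
- f = 0.20: 0.5 / (0.5 + 0.5 × 0.8) = 0.5 / 0.9 = 0.556, a false advantage of 5.6 points.
- f = 0.40: 0.5 / (0.5 + 0.5 × 0.6) = 0.5 / 0.8 = 0.625, a false advantage of 12.5 points.

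At p = 0.5 these losses are 0.20 × 0.5 = 10% and 0.40 × 0.5 = 20% of all bowel-first starters.

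**Step 2: does the method comparison reveal this?** Two groups were simulated (bowel-first and other) with a true sequence effect of zero, one measured factor x and one unmeasured factor u.
- Treatment: logit P(bowel-first) = −0.2 + 0.6x + a·u, with a = 0, or a = 0.8 for unmeasured confounding.
- Outcome: logit P(disease-free) = −0.2 − 0.5x − 0.8u.
- Selection: each failing bowel-first patient is dropped before enrolment with probability f.
- GLM: logistic regression on sequence and x, standardised to a risk difference in the bowel-first patients.
- Matching: 1:1 nearest neighbour, caliper 0.2 SD of the logit propensity score; the estimate is the mean within-pair difference.

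Risk difference in disease-free proportion, bowel-first minus other, at n = 150 (600 replicates):

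| Scenario | GLM | Matching | Mean absolute gap |
|---|---|---|---|
| No bias | +0.003 | +0.005 | 0.037 |
| f = 0.20 | +0.055 | +0.054 | 0.036 |
| f = 0.40 | +0.120 | +0.118 | 0.037 |
| Unmeasured confounding only | −0.116 | −0.117 | 0.035 |
| f = 0.40 plus unmeasured confounding | +0.004 | +0.005 | 0.038 |
| Misspecified x, poor overlap | −0.011 | −0.001 | 0.042 |

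Monte Carlo error on each mean is about 0.004 (for example 0.089/√600 for the GLM with no bias). In the first five rows the methods agreed within 0.10 in 95% to 97% of replicates, whether or not bias was present.

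**Step 3: larger samples.** At n = 3000 (15 replicates only) the biases persisted: +0.054/+0.055 for f = 0.20, +0.123/+0.121 for f = 0.40 and −0.117/−0.122 for unmeasured confounding. The gaps were 0.008 to 0.009, against 0.005 with no bias. That difference is trivial beside biases of 0.05 to 0.12. The misspecified case gave −0.008/+0.006 with a gap of 0.015. The comparison therefore responds to functional form and overlap, and not usefully to selection or unmeasured confounding.

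**Late entry** was not simulated. The argument there is logical: patients who enrol late are those who reached the regional MDT, and neither method contains those who did not.

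**The case against.** The strongest reply is that the protocol does not claim what a critic might attribute to it. The comparison is meant to explore, within an exploratory analysis, and nowhere is agreement said to show absence of bias. If spectrum bias means case mix and overlap among enrolled patients, the comparison has a legitimate use. Referral loss has its own section, which names the affected patients, undertakes to report the loss and limits reporting to description. The cohort is unpowered by design, and the observational limitation is stated at the front of the article. All of this stands and lowers the weight of the point.

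Four stronger readings are tempting but not supported:
- A reader might infer that the investigators will treat agreement as validation. That is a risk of misreading, not a stated plan.
- A reader might infer that bowel-first must look better. The protocol says only that non-referral is likely, and the late entrants it describes are typically emergency presentations whose prognosis may differ. In the simulation, unmeasured confounding produced the opposite sign and could cancel the referral bias.
- A reader might infer near-perfect agreement in the actual study. The averages agree closely, but within one cohort of 150 the two estimates differ by about 3.5 points.
- A reader might infer that matching will discard many patients. The protocol gives no matching ratio or caliper, so this cannot be said.

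The reply does not supply an analytic step that separates or bounds the acknowledged loss. Acknowledgement in the text and an adjusted comparison of sequences will sit side by side with nothing connecting them.

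**Conclusion.** The point holds in limited form. The GLM and propensity comparison is informative about model dependence and overlap on measured factors. It is uninformative about referral loss, late entry and unmeasured confounding. This follows from the two methods sharing patients and covariates, and does not depend on any assumed rate.

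The size does depend on assumptions. With no true effect and referral loss as the only bias, losing 20% or 40% of failing bowel-first patients gives a false bowel-first advantage of about 5 or 12 percentage points by either method. The simulation uses two groups where the plan has three, and the true loss rate is unknown. Neither the net direction nor the net size of bias in this cohort can be stated from the document.

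**What to change.** 1. State in Statistical methods that comparing GLM with propensity matching assesses overlap and model dependence on measured covariates only, and that agreement is not evidence against selection bias.

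2. Report the sequence comparison also in patients seen at the HPB MDT before any resection, and show those enrolled after bowel surgery separately. The referral loss described arises between local bowel-first surgery and the regional MDT, so patients seen before any resection have not passed through that filter.

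3. Add a tipping-point table over a range of assumed unreferred bowel-first progressors, for example 0–40%, showing where the observed difference would vanish or reverse. State the denominator. If f is the share of failing bowel-first patients, each observed bowel-first failure can be weighted by 1/(1 − f): 1/0.8 = 1.25 at 20% and 1/0.6 = 1.67 at 40%. This assumes that the missing failures resemble the observed ones on measured covariates.

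The cost is a sentence of wording and a few tables from data already being collected. The pre-resection comparison will contain fewer bowel-first patients, so its interval will be wider; the protocol gives no figure from which to say by how much.
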